### Intervention development

The technology for the gamified digital feedback intervention was developed in Germany and the content was developed by the whole research team. It is a child-centred smart hand hygiene intervention. The installations at each washbasin are IoT-based. Each installation will consist of a touchless faucet powered by a digital power box (a), a soap sensor (b), a feedback display (only for treatment groups) (c), and a gateway (d), which connects to the devices (a-c) via Bluetooth and relays data to a cloud infrastructure (e). Connected Information Systems (f), such as dashboards to monitor hand hygiene, can access the system via this cloud infrastructure [40] (Fig 5).

**Fig 5 pone.0280686.g005:**
[figure not shown]
Technical setup of the system.

The digital power box is a device developed by Amphiro AG that equips faucets with digital functionalities. The device will be installed between the water wall outlet and the faucet in the kindergartens. It measures, processes, and sends the individual water withdrawal data to an LTE Gateway. The energy required for its operation will be generated by an integrated micro-turbine, which eliminates the need for an external power supply (often unavailable at the installation site) or batteries (which need to be replaced regularly and are therefore impractical for many maintenance processes).

This study will use a well-tested technology. It is currently used in clinical settings to improve the hand hygiene of health care professionals. The technology was tested during a pre-study conducted in spring of 2021. This kind of similar live feedback approach used in the field studies has shown larger effects on routine behaviour [41]. The screen display will provide an educational video showing instructions on how to do handwashing when hands are dirty for the children to follow (Fig 6). The handwashing instruction was guided by the World Health Organization’s “How to Handwash” poster. When the handwashing is done correctly (based on the water and soap usage), a reward of animal animation will appear on the screen display (Fig 7). The live feedback display will enhance the children to do handwashing correctly, thus improving hand hygiene practices.

**Fig 6 pone.0280686.g006:**
[figure not shown]
The “How to handwash” content of the video on the screen display.

**Fig 7 pone.0280686.g007:**
[figure not shown]
The animal animation as a reward.

### Implementation

This study will be composed of three phases, the baseline, intervention, post-intervention, and a twelve-month follow-up (Fig 2). The first phase will be the baseline which will last for three weeks. The systems will be installed in the kindergarten sinks which will collect data from the handwashing activities, but it will not provide any feedback or screen activity. A “how-to” teaching session (video-based training) will be held in each kindergarten in the middle of the baseline phase for all children to learn the same hand hygiene information. The second phase will be the treatment and will last for three weeks. The third phase will be the post-intervention, and it will also last for three weeks. After this phase, the systems will be de-installed from all the kindergarten sinks. In Finland, there will be a twelve-month follow-up after the intervention.

The control group will have no screen display next to the sink throughout the study. The intervention A (instruction) group will receive instructions from the screen display next to each sink where handwashing instructions are shown during the handwashing activity but no reward after. The intervention B (reward) and intervention C (reward plus instruction) groups will receive instructions and rewards shown on a screen display right next to the sink during the intervention phase. In these groups, handwashing instruction is shown during the handwashing activity and if handwashing is done correctly (based on time and soap usage), a reward of animal animation is shown on the screen, see Figs 6 and 7. During the post-intervention phase, the intervention C group will remain to have the screen display receiving instructions with no reward. In Finland, sick leave days of the children and kindergarten staff will be tracked (Fig 8).

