### Hypotheses

Main effects: Control, Intervention A (instruction), Intervention B (instruction plus reward), and Intervention C (instruction plus reward and instruction in post-intervention phase) groups

H1: Feedback display will increase handwashing activity in the kindergarten (in the short term) during intervention phase
For intervention A, B, and C groupsFor intervention B and C groups more than intervention A groupH2: Handwashing activity in the kindergartens will decline with time (while the display will still be turned on)
For intervention A group less than intervention B and C groups during the beginning of the post-intervention phaseFor intervention B group less than intervention C group during post-intervention phase.For control group less than intervention A, B, and C groups in all phases.Motivation crowding out: Measurement-basedH3a: Effect will partially persist, when feedback display in kindergarten will be turned off during the beginning of post-intervention phase. For intervention C groups less than intervention A and B groups. (Explanation: habit will be formed, there will be partial motivation crowding out, impact in increased self-efficacy will be stronger)H3b: Effect will vanish and handwashing will return to baseline behaviour for intervention B group in post-intervention phase. (Possible explanation: no habit will be formed, there will be no motivation crowding out)H3c: Effect will vanish and handwashing activity will drop below baseline behaviour for intervention A group in post-intervention phase. (Possible explanation: there will be crowding out)
Acquisition of competences and self-efficacy: Intervention A, B, and C groupsH4a: Feedback intervention will increase competences and self-efficacy level of children after the intervention phase–for intervention B and C groups stronger than for intervention A groupH4b: Feedback intervention will increase competences and self-efficacy level of children after post-intervention phase–for intervention C group stronger than for intervention B group and for intervention B group stronger than for intervention A group.

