### Data collection

This study will start in mid-year of 2022 and will last for a year. The data will be analysed using quantitative and qualitative methods. The child’s age and gender will be collected. The implementation phases and timeline of the data collection are shown in Figs 1 and 2.

The handwashing activity data from the system will be recorded every day during the baseline, intervention, and post-intervention phases. The parent survey data will be given and collected within the last week of the intervention phase. The kindergarten staff interview data will be collected during the last week of the intervention phase and right in the beginning week of the post-intervention phase to evaluate the observed effect of children’s hand hygiene behaviour and reactions towards the removal of the instructions and reward. The children’s observation sessions and interviews will be collected during the last weeks of the baseline, intervention, and post-intervention phases. The number of sick leave days will be collected from the sick leave records provided by the kindergarten staff one year before and after the start of the baseline phase.

The follow-up strategy will include sending updates of the study phases through email to the kindergarten managers and staff. The email includes the details of reminding how and when the participants will be contacted for follow-up. It will also include updates on the contact information of the participants.

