### Data analyses

Data will be analysed using qualitative and statistical methods. All eligible participants will be included in the analysis. The statistical analyses will be performed with R. The categorical and numerical data will be analysed using one-way analysis of variance (ANOVA). Qualitative analysis will be presented thematically [42].

For the measurement data from the system:

Data pre-processing: Data will be investigated where water and soaping data are combined to single handwashing procedures. Data points that are not valid (outside of kindergarten opening hours) will be removed. The descriptive statistics of the clusters, randomization checks, ICC (intracluster correlation) will be calculated. The data will be analyzed using linear fixed-effect regression model for panel data, and dependent variable soaping time. The four groups will be compared in baseline, intervention, and post-intervention phases.

For the survey and staff interview data:

The comparison among the groups will be implemented using random effects regression, allowing for the clustered nature of the data, and adjusted using the covariates of the adjusted analyses (when a small number of clusters are present) [43]. Simple bias analysis will be used to quantify the uncertainty of the biases such as confounding variables [33]. The qualitative results of the survey and kindergarten staff interview will be analysed and compared thematically. The four groups will be compared after intervention phase.

For the children interview and observation data:

The analyses will be compared among groups based on the complete data only. The comparative analyses approach used to calculate the observation, survey, and staff interview will be used. The self-efficacy measurement scale will be developed and evaluated for its psychometric properties [44,45]. The qualitative result of the observation and interviews will be analysed and compared thematically [42]. Children who will participate the interview at one time point will be considered as missing data, these will be excluded from the analysis. The four groups will be compared in baseline, intervention, and post-intervention phases.

For the sickness day data:

The total sick leave days are compared among the groups one year before and after the start of the baseline phase.

The statisticians of the two universities will validate the statistical results of the data.

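### The handwashing lesson in the middle of baseline leaves H3b and H3c, and a within-arm reading of H3a, without a clean reference level.

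*Protocol article*

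**What the plan says.** Implementation sets the length of the phase: "The first phase will be the baseline which will last for three weeks". The same section says that the how-to session "will be held in each kindergarten in the middle of the baseline phase for all children to learn the same hand hygiene information", so the control kindergarten is taught as well.

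Data collection states: "The handwashing activity data from the system will be recorded every day during the baseline, intervention, and post-intervention phases". The sensor baseline therefore spans the lesson. Data analyses names one exclusion for sensor data: "Data points that are not valid (outside of kindergarten opening hours) will be removed". It then specifies a fixed-effect panel regression of soaping time and a comparison of the four groups in each of the three phases. It does not mention the lesson.

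Two hypotheses use baseline as their yardstick. H3b reads: "Effect will vanish and handwashing will return to baseline behaviour for intervention B group in post-intervention phase". H3c predicts that "handwashing activity will drop below baseline behaviour for intervention A group in post-intervention phase". The Hypotheses section links the first outcome to an absence of motivation crowding-out and the second to its presence. H3a predicts that the effect partly persists once the display is off. It can be read within an arm, although its second sentence compares arms.

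The child-level measures are timed differently. The children's "observation sessions and interviews will be collected during the last weeks of the baseline, intervention, and post-intervention phases", so their baseline lies after the lesson.

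**The concern.** The lesson is meant to change the behaviour that the sensors measure. Days before it show untaught children and days after it show taught children. A baseline level taken over the whole phase averages the two and describes neither.

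This matters most for crowding-out, which is a stated objective. H3b and H3c differ only in whether an arm ends at its baseline level or below it. If that level is displaced by an unknown fraction of the lesson's effect, an arm can be placed on the wrong side of it although the display did nothing of the kind. The interviews and observations use the taught state as baseline, so the word baseline also means different things for different outcomes.

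**Working it through.** The documents give no lesson effect and no retention figure, so there is no figure of the plan's to reproduce on this point. Results are in units of the lesson effect.

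**Inputs**
- Baseline of three weeks with the lesson at its middle (Implementation).
- Daily sensor recording and no split at the lesson (Data collection; Data analyses).
- Pre-study: 10,000 handwashing events in 42 days over four clusters, two treated and two control (Sample size).
- Assumed: five opening days a week, so 15 baseline days. A lesson after day 7, 8 or 9 gives a taught share s of 8/15 = 0.53, 7/15 = 0.47 or 6/15 = 0.40. I use s = 0.5 with a range of 0.4 to 0.6.
- Unknown: d, the lesson's effect on soaping time, and r, the share of d still present post-intervention.

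**Step 1: an arm with no display carry-over and no crowding-out.** Let b be the untaught level.
- Pooled baseline = (1 − s)b + s(b + d) = b + s·d
- Post-intervention level = b + r·d
- Apparent change from pooled baseline = (r − s)d

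| Retained share r | s = 0.5 | s from 0.4 to 0.6 |
|---|---|---|
| 1 (fully kept) | +0.5d | +0.6d to +0.4d |
| 0.5 | 0 | +0.1d to −0.1d |
| 0 (fully lost) | −0.5d | −0.4d to −0.6d |

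The true display-related change is zero in every cell.

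**Step 2: an arm with real crowding-out c below the taught level.** With r = 1 and s = 0.5, the apparent change is −c + 0.5d. At c = 0.5d this is exactly 0: H3c would miss the fall, and the arm would be read as having returned to baseline.

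**Step 3: changing only the reference window.** Against post-lesson days alone, the change in Step 1 becomes (b + r·d) − (b + d) = (r − 1)d. This is 0 if r = 1 but −d if r = 0. It is larger in size than (r − 0.5)d whenever 1 − r > r − 0.5, that is, r < 0.75.

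**Step 4: contrast with control.** If d and r are the same in both arms, the change minus the control arm's change is (r − 1)d − (r − 1)d = 0 for the post-lesson reference. The pooled reference likewise gives 0. Real crowding-out of c shows as −c. If the lesson effects differ by Δ, the residual is (r − 1)Δ for the post-lesson reference and (r − 0.5)Δ for the pooled one.

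**Step 5: data left in a post-lesson window.** 10,000 / 42 / 4 = 59.5 washes per kindergarten per day, assuming equal clusters.
- If the 42 days are calendar days, half the baseline is 10.5 days: 59.5 × 10.5 = 625.
- If they are opening days, half is 7.5 days: 59.5 × 7.5 = 446.

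**The case against.** The strongest reply is that the lesson reaches every kindergarten, control included, and that the planned comparison is among the four groups. In such a contrast the lesson cancels if its effect is equal across arms (Step 4). That stands. A reader might infer that the lesson's effect will be credited to the display throughout, or that H1 is biased. The documents do not support this: H1 and the between-arm parts of H2 and H3a are largely protected.

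A second reply is that the article never says the baseline is a three-week mean. Daily panel data allow day or period terms, and an unseen analysis plan may contain them. This has some force: pooling is inferred from daily recording, a single exclusion rule and comparison by phase. But the lesson's place inside the phase and the within-arm wording of H3b and H3c are fixed in the article, and nothing there points to a split.

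A third reply concerns direction. It is tempting to say that the mixed baseline always flatters persistence and hides crowding-out. That holds only if the lesson is largely retained; with enough fading, the error reverses. By the same algebra, moving the baseline window alone could make matters worse.

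Finally, the different baselines for sensors and interviews do little harm in themselves. These are separate outcomes with separate analyses, and no hypothesis subtracts one from the other.

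**Conclusion.** The concern holds for H3b, for H3c and for H3a if read within an arm. As written, their reference level mixes untaught and taught behaviour. With the lesson at mid-phase, the error for an arm with no carry-over and no crowding-out is about (r − 0.5)d, anywhere from −0.5d to +0.5d. It can hide crowding-out, look like persistence or look like crowding-out.

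This rests on three assumptions: that the lesson changes soaping time at all, that about half the baseline is taught, and that baseline is taken over the whole phase. The error in seconds cannot be computed because d is not given. It does not extend to a general bias in the trial's comparisons between arms, provided the lesson works similarly in each. That condition can hardly be checked here: Sample size plans three kindergartens for four groups, with one kindergarten covering two intervention groups. The point should be settled before analysis, but it does not threaten the main comparison.

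**What to change.** In the sensor panel model:

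1. Code the baseline days before the lesson as a separate period, and use the days after the lesson up to display switch-on as the reference for H3a to H3c. This also allows the lesson's effect to be estimated and brings the sensor baseline into line with the interviews and observations.
2. Test H3b and H3c as the arm's change from that reference relative to the control arm's change over the same periods, so that fading of the lesson cancels. Step 3 shows why the new window should not be adopted without this contrast.
3. Report the pooled-baseline result as a sensitivity analysis.

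No change to conduct and no new data are needed. About half the baseline days remain as reference, roughly 450 to 625 washes per kindergarten at the pre-study rate. The contrast with control adds some variance and assumes a similar lesson effect across arms, and the report should say so. Fixing the window in advance also removes the freedom to choose it after seeing the data.

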**Fig 8 pone.0280686.g008:**
[figure not shown]
Flowchart of the cluster randomization.

To improve the adherence of the participants to the study, the research team will maintain the engagement, encourage retention, and thank the kindergarten managers, staff, children, and parents. Named persons from the researcher team call and pay visits to the study settings every now and then if the kindergarten personnel permits. Contact information of the research team will be provided to the kindergarten staff and parents before the trial. The participants will be reminded through email about the oncoming surveys and interviews, and they will be updated about the progress of the study.

### Data collection

This study will start in mid-year of 2022 and will last for a year. The data will be analysed using quantitative and qualitative methods. The child’s age and gender will be collected. The implementation phases and timeline of the data collection are shown in Figs 1 and 2.

The handwashing activity data from the system will be recorded every day during the baseline, intervention, and post-intervention phases. The parent survey data will be given and collected within the last week of the intervention phase. The kindergarten staff interview data will be collected during the last week of the intervention phase and right in the beginning week of the post-intervention phase to evaluate the observed effect of children’s hand hygiene behaviour and reactions towards the removal of the instructions and reward. The children’s observation sessions and interviews will be collected during the last weeks of the baseline, intervention, and post-intervention phases. The number of sick leave days will be collected from the sick leave records provided by the kindergarten staff one year before and after the start of the baseline phase.

The follow-up strategy will include sending updates of the study phases through email to the kindergarten managers and staff. The email includes the details of reminding how and when the participants will be contacted for follow-up. It will also include updates on the contact information of the participants.

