### Limitations

The intervention, technology and experimental setup were evaluated in a pre-study. The pre-study showed promising results with regards to main effects: a statistically significant increase in handwashing time was observed in the treatment kindergarten. Minor issues and challenges that were encountered in the pre-study are considered and improved in the presented study here diminish existing limitations. Especially the technical hardware was improved to diminish the risk of hardware failures and outages. Furthermore, a research member is assigned to address the technical issues during the study immediately, if any issues happen. A possible limitation is the Hawthorne effect when observing the handwashing activity, as individuals might change their behaviour when knowing that they are being observed. To manage this, the observers will not be informed the participants when and where the observation sessions take place, and during the observations, they will be informed that the focus is on hand hygiene in general. Another limitation is the ongoing Covid-19 pandemic, as it can affect the collection of sick leave days for the children and kindergarten staff. To minimize this, sick leave data one year before the baseline phase will be obtained from the record of the kindergarten. Covid-19 also affect the children’s hand hygiene behaviour and performance. Thus, there will be four different groups to be compared in three timepoints and a 12-month follow-up.

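### Observation sessions fall in the last week of each phase and observed washes are not separated in the sensor data, so an observer effect can distort the H2 trend and the H3a switch-off contrast unless it is equal across arms

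*Protocol article*

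**What the plan says.** Under Data collection, the article states that "The handwashing activity data from the system will be recorded every day during the baseline, intervention, and post-intervention phases". The same section places the children's sessions at the end of each phase: "observation sessions and interviews will be collected during the last weeks of the baseline, intervention, and post-intervention phases". Implementation gives the phase length ("The first phase will be the baseline which will last for three weeks") and the same duration for the other two phases, so the observed week is one third of each. Outcome measures says that assistant researchers watch the children during handwashing in the kindergarten. A watched wash is therefore also a sensor wash.

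For the sensor data, Data analyses names one exclusion: "Data points that are not valid (outside of kindergarten opening hours) will be removed". The model is a linear fixed-effect panel regression on soaping time that compares the four groups in each phase. No term for observed periods is mentioned.

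Limitations names the problem: "A possible limitation is the Hawthorne effect when observing the handwashing activity", because "individuals might change their behaviour when knowing that they are being observed". The stated safeguard is that "the observers will not be informed the participants when and where the observation sessions take place", which I read as sessions being unannounced. Participants are also told that the topic is hand hygiene in general.

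Two hypotheses depend on when washes occur within a phase. H2 predicts that washing falls off over time even with the screen still on. H3a concerns what remains at the start of the post-intervention phase. H3b and H3c compare the post-intervention phase with baseline.

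**The concern.** The safeguard addresses anticipation, not presence. An unannounced observer is still visible once there, and telling children that the subject is hand hygiene may itself prompt washing. Nothing stated protects the sensor record, so washes performed under observation enter the primary data unmarked.

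The timing matters because observation is concentrated in the last third of each phase. For H2, observation would push soaping time up in the week where the decline should be deepest. For H3a, the last intervention week contains observation sessions and the first post-intervention week does not, so part of any fall at switch-off could come from the observer leaving rather than from the display going dark. At stake is whether a flat trend is read as no habituation, and whether an ordinary return to unobserved behaviour is read as loss of effect.

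**Working it through.** **What the plan gives.** It states no size for the observer effect, no number of sessions and no share of washes observed, so there is no figure of its own to reproduce on this point. The one planned figure used is the number of kindergartens. From Sample size: design effect 1 + (40 − 1) × 0.062 = 3.418; 31 × 3.418 = 105.96, i.e. the stated 106 (the 4.418 printed in that product is a misprint); 106 / 40 = 2.65, rounded up to three kindergartens. Three kindergartens for four groups means about one per arm.

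**Direction.** Let h be the amount by which observation raises mean soaping time in week 3 of a phase, with no other change. The weekly shifts are (0, 0, h) in each phase.
- Intervention week 3 minus week 1: +h (least-squares weekly slope +h/2).
- First post-intervention week minus last intervention week: 0 − h = −h.
- First post-intervention week minus baseline mean: 0 − h/3 = −h/3.
- Whole post-intervention mean minus whole baseline mean: h/3 − h/3 = 0.

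**Comparison with control.** Suppose a true decline of 2 units from week 1 to week 3 in an intervention arm and none in control.
- Within the arm, the apparent change is −2 + h: −1, 0 and +2 for h = 1, 2 and 4.
- Relative to control with the same h, it is (−2 + h) − h = −2 for every h.
- If the effect in control is half as large, it is (−2 + h) − h/2 = −1.5, −1.0 and 0 for h = 1, 2 and 4.

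Equality must also hold on the scale of the model. If observation lengthens washes by the same percentage everywhere, the arm with longer washes gains more seconds, and the effect does not cancel in a linear model for soaping time.

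**Size (assumptions throughout).** Let f be the share of last-week washes observed and e the relative lengthening of an observed wash. The last-week mean is inflated by f·e. With no true change, the false fall into the next week is 1 − 1/(1 + f·e), and the false fall of early post-intervention against the baseline mean is 1 − 1/(1 + f·e/3).

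| f | e | Last-week inflation | False step | Against baseline mean |
|---|---|---|---|---|
| 8% | 10% | 0.8% | 0.8% | 0.3% |
| 8% | 20% | 1.6% | 1.6% | 0.5% |
| 8% | 30% | 2.4% | 2.3% | 0.8% |
| 25% | 20% | 5.0% | 4.8% | 1.6% |
| 50% | 20% | 10.0% | 9.1% | 3.2% |
| 50% | 30% | 15.0% | 13.0% | 4.8% |

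The 8% comes from the pre-study in Sample size: 10,000 events in 42 days (6 weeks) over four clusters is 10,000 / (6 × 4) = 417 per cluster-week, for (82 + 53) / 4 = 34 children per cluster. If each child is observed washing once per phase, f = 34 / 417 = 8%. If the 42 days were five-day-week opening days (8.4 weeks), there would be 10,000 / (8.4 × 4) = 298 events per cluster-week and f = 34 / 298 = 11%. Shares of 25% and 50% would need about 3 and 6 observed washes per child in that week (0.25 × 417 / 34 and 0.50 × 417 / 34).

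For H2, a true 10% within-arm decline would show as 1 − 0.90 × 1.016 = 8.6% at f = 8%, e = 20%, and as 1 − 0.90 × 1.10 = 1.0% at f = 50%, e = 20%.

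**The case against.** The strongest reply is the control arm. All groups share one observation schedule, the analysis compares four groups in each phase, and much of H2 and H3a is worded as one arm against another. An equal observer effect then drops out of trends and steps as well as phase means. This stands. A reader might infer that H2 and H3a have no protection at all. The documents do not support that, because bias in a controlled contrast needs an effect that differs by arm. What remains is that the hypotheses also speak of decline and persistence within a group, and that with about one kindergarten per arm a kindergarten-specific reaction to observers cannot average out.

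A reader might also infer that observation could produce the drops predicted under H3b and H3c. It does not in whole-phase contrasts, since baseline and post-intervention each contain an observed last week. Nor does the article state a test of the last intervention week against the first post-intervention week.

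The large percentages rest on observed shares that look high against the pre-study event count, so a false fall of 5% to 9% should not be presented as the expected size. The article names the Hawthorne effect for observation only, so I do not count the child interviews. It does not say that assistants stand at the sink. Staff interviews also run in the first post-intervention week, so that week is not free of study contact.

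Finally, a condensed article may leave model terms and sensitivity analyses to a fuller document, and the absence of such a term is not a fault in itself. But the article fixes the overlapping schedule and sets out how it manages the Hawthorne effect. Session times not recorded during the trial cannot be recovered by a later analysis plan.

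**Conclusion.** The concern holds in limited form. Observation overlaps the sensor record in the last week of every phase, and nothing stated separates the observed washes. A positive last-week effect h biases a within-arm H2 change by +h, the switch-off step by −h, and early post-intervention against the baseline mean by −h/3. It leaves whole-phase H3b and H3c contrasts, and comparisons with control, unbiased if it is equal across phases and arms. That condition cannot be taken for granted with so few kindergartens.

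The size is not derivable from the documents. Under an assumed effect of 10% to 30% and an observed share of 8% to 50%, the false step is about 1% to 13%, and one observed wash per child per phase would put it near 1% to 2%. The problem is probably small. It is worth correcting because the correction is cheap and must be in place before data collection.

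**What to change.** - Have the assistant log the sink and the start and stop time of each observation session, in the same way in all arms and phases. The sensor events already carry start and end times, so they can be matched to these windows. Log the session window only, not each child's wash, so that the article's assurance that sensor data allow no conclusions about individuals still holds.
- Add an observed-window indicator to the soaping-time model, or pre-specify a sensitivity analysis without those windows. A single indicator assumes one effect in all arms, so check it by arm as well.
- Base H2 and H3a on changes relative to control.
- Keep all events in the primary data set. Removing the windows from it would change the mix of washes in the last week only, for example if sessions coincide with routine group washing, and could create its own last-week artefact.
- Report observed against unobserved washes of the same week as an estimate of the Hawthorne effect. Carry-over within the week would make this an underestimate.

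The cost is one checklist line per session and a little extra analysis, with no extra visits.
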